### Theoretical Framework

The Remote Assessment of Lung Disease and Impact on Physical and Mental Health (RALPMH) study will use a prospective cohort study framework. This will leverage our RADAR-Base software platform and existing experience working on remote monitoring projects, such as RADAR-CNS [18], and take a similar approach to the major depressive disorder protocol [19]. In addition to this, we have recently developed RADAR-Base capabilities to deliver notifications dependent on real-time processing of participant data streams. This module of RADAR-Base will be evaluated here by deploying an exacerbation detection algorithm (using HR, SpO_2_, and other measures), and participants will be asked in near real time to confirm/reject and score the algorithm’s assertion via a short questionnaire, the Exacerbation Rating Scale (ERS), close to or during the period of exacerbation, in order to provide accurate feedback independent of recall. The ERS scoring will be used to evaluate the algorithm sensitivity/specificity and to evaluate options for personalized exacerbation detection.

Previous studies [12,13] on exacerbations in COPD found that changes in resting heart rate (RHR), pulse oxygen saturation (SpO_2_), and peak airflow are highly correlated with symptoms before, during, and after exacerbation onset, as shown in Figure 1.

Another study [20] looked at the identification and subsequent prediction of exacerbations in COPD. The authors used features derived from pulse oximeters to predict exacerbations using logistic regression. They found that all three vital signs (oxygen saturation, pulse rate, and respiratory rate) are predictors of exacerbations, with oxygen saturation being the most predictive. Another study [21], which looked at the correlation between RHR and acute exacerbations in COPD, found that patients with a higher RHR following exacerbation demonstrated an increased risk of exacerbation.

There is evidence in the literature that pulmonary diseases, like COPD, lung fibrosis, etc, are closely related to the heart [22]. Pulmonary vascular abnormalities are frequently present in patients with respiratory disorders. Similar correlations were found with HR in severe acute respiratory syndrome (SARS), where patients were found to have a high HR and low blood pressure [23].

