#### Assess the Potential of Remote Monitoring in COPD, IPF, and COVID-19

The potential of remote monitoring will be evaluated in the context of cardiopulmonary disorders. This will involve developing methods to quantify disease trajectory as compared with standard clinical measures (in IPF, these would be changes in forced vital capacity and death); detecting exacerbations/symptoms, such as changes in wearable data (eg, HR, SpO_2_, and activity), during the reported period of exacerbation (a real-time algorithm will be included to predict exacerbations with patients notified with the ERS to confirm the prediction at or close to the time of the event); detecting exacerbations prior to or after the reported period of exacerbation (eg, a signal that may precede participant awareness of the exacerbation/symptom); detecting subclinical exacerbations in patients with lung fibrosis; tracking self-reported symptoms and outcomes (including precursor presymptomatic signals) and their frequency and order; and reporting longitudinal mental health symptom measures, as reported by the Generalized Anxiety Disorder scale (GAD-7) and Patient Health Questionnaire depression scale (PHQ-8), associated with the three diseases. This will provide the potential to assist with future applications around disease self-management. In the case of the posthospitalization COVID cohort, we will assess whether remote monitoring can be used as a symptom collection tool and as a long-term low-burden monitoring solution. Fatigue will be assessed by Garmin Body Battery values and the Fatigue Severity Scale, while long-term COVID impairments will be measured weekly using the Centers for Disease Control and Prevention (CDC) COVID-19 long-term effects (CCLTE) list, World Health Organization (WHO) symptoms list, and post-COVID functional status (PCFS), a COVID-19-specific widely used questionnaire on health-related impairments (physical functioning scale).

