**Questionnaires - Symptoms, mental health, quality of life (QoL) (aRMT)**					
	Post-COVID-19 functional status (PCFS) scale	Questionnaire/aRMT phone app	Weekly	COVID-19	Establish post COVID-19 functional status [36].
	CDC COVID-19 long-term effects (CCLTE) (aRMT)	Questionnaire/aRMT phone app	Daily	COVID-19	Establish the degree of long-term COVID-19 effects [15].
	WHO COVID-19 symptoms (WCS) list (aRMT)	Questionnaire/aRMT phone app	Daily	COVID-19	Establish the degree of persistent COVID-19 symptoms [37].
	COPD assessment test (CAT)	Questionnaire/aRMT phone app	Cohort: Daily	All	CAT to measure the impact of COPD on a person’s life. It is unidimensional, and assesses cough, sputum, dyspnea, and chest tightness. Eight questions [38,39].
	Idiopathic pulmonary fibrosis patient-reported outcome measure	Questionnaire/aRMT phone app	Weekly	Interstitial lung disease (ILD)	ILD QoL self-report.
	Living with idiopathic pulmonary fibrosis	Questionnaire/aRMT phone app	Daily	ILD	ILD QoL self-report.
	Visual analog scale (VAS) cough	Questionnaire/aRMT phone app	Monthly	ILD	Score symptoms (cough).
	St. George’s Respiratory Questionnaire (SGRQ)	Questionnaire/aRMT phone app	Quarterly	All	Assess the impact of overall health, daily life, and well-being in patients.
	Pittsburgh Sleep Quality Index (PSQI)	Questionnaire/aRMT phone app	Monthly	ILD	Sleep scoring questionnaire.
	Exacerbation rating scale (ERS)	Questionnaire/aRMT phone app	Dynamic/on demand	All	A confirmatory rating scale for detected exacerbations in real time; participants will be sent notifications to complete these.
	Generalized Anxiety Disorder scale (GAD-7) and Patient Health Questionnaire depression scale (PHQ-8) (aRMT)	Questionnaire/aRMT phone app	Fortnightly	All	Establish depressive and anxiety symptoms [40,41].

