We will use the pulse-respiration quotient [44] and pulse-activity quotient as measures of the changes in respiration efficacy and exacerbation.

We will adopt machine learning approaches to perform both cross-sectional and individualized classification for the identification of events, such as exacerbations, using a questionnaire or other active data as labels providing context to passive data streams such as HR, SpO_2_, respiratory rate, and others.

Using multimodal data sets, we will characterize the periods of time around acute events, such as exacerbations, to include the pre-exacerbation period, period during exacerbation, and postexacerbation period.

We will investigate the potential of the data collected to identify putative subclinical exacerbations or other lower level fluctuations in participant symptoms.

If adequate numbers of events are generated in the study, an opportunity to apply anomaly/novelty detection methods will be possible. In this way, we will use these approaches to learn the baseline state for the participants and establish significant deviations from this.

Using the real-time aspect of the data collection, we will use the real-time ERS to acquire real-time responses to evaluate and assess the performance of a model for exacerbation detection and refine an individual-level model for exacerbation detection.

Since we do not have enough prior data, we plan to consider real-time anomaly detection methods and preprocess the data based on prior knowledge. The models will be pretrained on a daily schedule (using previous N days of data; N is yet to be decided but is initially considered 21 days) and will be ready for running inferences in real time (using wearable sensor data as inputs collected in real time) and taking actions based on the results of the inferences (sending an ERS assessment through the aRMT app) to acquire responses at the time of the event to assess the performance of the model.

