##### COPD

We will recruit 20 patients with COPD from our services in London and follow them for up to 6 months or until the first exacerbation, whichever is sooner. We will recruit patients with a history of exacerbations to increase the likelihood of identifying patients who would experience events during the study. We will analyze whether monitoring is able to detect exacerbations earlier than the current gold standard (patient reporting to a clinician) and therefore could be used to help patients get treatment earlier.

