**Figure 3 figure3:**
[figure not shown]
Study flow diagram. CAT: COPD assessment test; CCLTE: CDC COVID-19 long-term effects; COPD: chronic obstructive pulmonary disease; EoP: experience of participation; ERS: Exacerbation Rating Scale; FSS: Fatigue Severity Scale; GAD-7: Generalized Anxiety Disorder scale; ILD: interstitial lung disease; IPF: idiopathic pulmonary fibrosis; l-IPF: living with idiopathic pulmonary fibrosis; KBILD: The King's Brief Interstitial Lung Disease; MRC: Medical Research Council; PCFS: post-COVID function status; PHQ-8: Patient Health Questionnaire depression scale; PROM: patient-reported outcome measure; PSQI: Pittsburgh Sleep Quality Index; RADAR: Remote Assessment of Disease and Relapse; SGRQ: St. George's Respiratory Questionnaire; TAMF: Technology Acceptance Model Fast Form; VAS: visual analog scale; WCS: World Health Organization COVID-19 symptoms.

The wearable device provided to participants connects to the wearable vendor’s application, and the data are uploaded to the vendor’s server, which is then synchronized to the RADAR-Base platform. On getting all the data, the RADAR-Base platform runs real-time data processing, and based on a threshold for exacerbation, it sends a notification and assessment for confirmation of the exacerbation in the form of the ERS. On exit or completion of the study, the participants will be asked about their experiences with the technology and the study.

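### ERS answers collected only after an alert cannot identify the algorithm's sensitivity; they give PPV and a false-alert rate, and the sentence promising sensitivity/specificity should be changed

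*Protocol article*

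**What the plan says.** The protocol article, under Theoretical Framework, sets the purpose: "The ERS scoring will be used to evaluate the algorithm sensitivity/specificity and to evaluate options for personalized exacerbation detection".

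Five places describe when the ERS is issued or what it is for:

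- Theoretical Framework: "participants will be asked in near real time to confirm/reject and score the algorithm’s assertion via a short questionnaire".
- Outcomes, on the potential of remote monitoring in the three diseases: "patients notified with the ERS to confirm the prediction at or close to the time of the event".
- Table 2, ERS row: "A confirmatory rating scale for detected exacerbations in real time; participants will be sent notifications to complete these", with collection frequency "Dynamic/on demand".
- Data Analysis: "taking actions based on the results of the inferences (sending an ERS assessment through the aRMT app".
- Study Flow Chart, text under Figure 3: "based on a threshold for exacerbation, it sends a notification and assessment for confirmation of the exacerbation in the form of the ERS".

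None of them sends the ERS on a schedule, on randomly chosen days without an alert, or after an exacerbation learned of in another way.

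The article also plans sources that do not depend on the alert. For COPD (Participant Cohorts) it will study whether monitoring can "detect exacerbations earlier than the current gold standard (patient reporting to a clinician"). Clinical Data provides for consented medical records, and Table 2 lists daily symptom questionnaires. None of these is linked to the sensitivity/specificity evaluation.

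**The concern.** Sensitivity is the share of true exacerbations that the algorithm flags, so it needs a count of those it did not flag. Specificity needs a count of stable periods without an alert. An instrument sent only after an alert labels neither group. In diagnostic-accuracy terms, only test positives are verified.

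The label is also not blind to the test: the participant is shown the algorithm's conclusion and asked to accept or reject it. Even the confirmed share may therefore be shifted, in a direction the documents do not let us predict.

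What is at stake is the stated evaluation of the real-time module. A sensitivity quoted from ERS answers would have no basis. Data Analysis also plans to refine individual-level models with ERS responses; on those labels alone, such models can learn from rejected alerts but never from missed events.

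**Working it through.** The article states no sensitivity, specificity or alert rate, so there is no figure to reproduce. The check is which cells of the two-by-two table the ERS fills.

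**Cells.** Alert confirmed = TP, observed. Alert rejected = FP, observed. No alert during an exacerbation = FN, no ERS. No alert while stable = TN, no ERS. Only the sum FN + TN is known, from monitored time.

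**Formulas.** PPV = TP/(TP+FP). Sensitivity = TP/(TP+FN). Specificity = TN/(TN+FP).

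**Inputs.** From the article: 20 COPD participants (Sample Size) followed for up to 6 months (COPD cohort). Assumed for illustration: 182 days each, so 20 × 182 = 3,640 participant-days as an upper limit; the participant-day as unit; TP = 10, FP = 10; every prompt answered.

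| FN (assumed) | TN = 3,640 − 20 − FN | PPV | Sensitivity | Specificity |
|---|---|---|---|---|
| 0 | 3,620 | 0.50 | 1.00 | 0.997 |
| 5 | 3,615 | 0.50 | 0.67 | 0.997 |
| 10 | 3,610 | 0.50 | 0.50 | 0.997 |
| 30 | 3,590 | 0.50 | 0.25 | 0.997 |
| 90 | 3,530 | 0.50 | 0.10 | 0.997 |

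The ERS data are identical in every row, so they cannot tell these sensitivities apart.

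**Bounds with no assumption on FN.** Sensitivity lies between 10/(10 + 3,620) = 0.003 and 1.00. Specificity lies between 0 and 3,620/3,630 = 0.997.

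**Specificity.** It is nearly constant in the table because FN is small beside 3,620. That stability comes from assuming that exacerbation days are rare and from counting in days, not from the ERS. What is observed directly is the false-alert rate, here 10/3,640 = 0.0027 per participant-day.

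**Prompt count for the optional addition in the fix.** COPD follow-up ends at the first exacerbation. At an assumed 2 exacerbations per year at a constant rate, over half a year:

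- Probability of a first event = 1 − e^(−1) = 0.632, so 20 × 0.632 = about 12.6 events.
- Mean follow-up = 0.632/2 = 0.316 years, about 115 days or 16.5 weeks.
- One prompt per participant per week: 20 × 16.5 = about 330 prompts.
- Treating these as a simple random sample at a specificity of 95%: SE = √(0.95 × 0.05/330) = 0.012, about 1.2 points before clustering. This is a rough guide; a weighted estimator that also uses the fully counted alerts will differ.

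**The case against.** **Other references are planned.** The article says that ERS scoring will be used for sensitivity/specificity, not that it is the only reference. Outcomes plans detection during, before and after reported exacerbations, Data Analysis uses questionnaires as labels, and the COPD cohort text names reporting to a clinician as the gold standard. This stands. A reader might infer that the study cannot estimate sensitivity at all; the documents do not support that. What remains wrong is attaching these measures to the ERS.

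**Nothing prescribes a table limited to alert days.** This also stands. A reader might infer that the plan forces a sensitivity of 100% and a specificity of 0%. Those values would arise only if someone tabulated alert days alone, which the article nowhere asks for. The accurate statement is that sensitivity is not estimable from these data. Nor is PPV the only thing they yield: monitored time adds a false-alert rate.

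**The prompts may not be limited to alerts.** Active Data Collection mentions dynamic notifications to validate classification without saying what triggers them, and Table 2 has "Dynamic/on demand". This is weak: neither provides for prompts without an alert, and the same Table 2 row describes notification for detected exacerbations.

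**The sentence is in the Introduction, and an article condenses.** Data Analysis speaks only of assessing model performance, which PPV and false alerts would satisfy, and it refers to an appendix on algorithms that is not shown. That lowers the weight of the point. It does not reconcile a consistently described trigger with a stated measure that the trigger cannot supply.

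**The illustration is extreme for COPD.** If follow-up stops at every participant's first exacerbation, there are at most 20 episodes. Ten confirmed would leave at most 10 missed, so episode-level sensitivity would lie between 0.50 and 1.00. That is fair, but the limit comes from the follow-up rule rather than the ERS, and the range is still too wide to be useful.

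**Conclusion.** The point holds for what alert-triggered ERS answers can estimate. They give PPV, subject to cueing and to unanswered prompts, and a false-alert rate per monitored time. They approximate specificity only under an outside assumption that exacerbation days are rare. They do not identify sensitivity, and a larger sample would not change that.

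The conclusion rests on the described trigger and on no assumed number. The counts 10, 10 and 0 to 90 only illustrate it: PPV stays at 0.50 while sensitivity runs from 1.00 to 0.10.

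The weight is moderate. The study is primarily about feasibility and acceptability, event detection is exploratory, and participants are told that their data will not trigger clinical action. The sentence should be corrected, but the study does not depend on it.

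A reader sizing the optional prompts might multiply 20 participants by 26 weeks. COPD follow-up ends at the first exacerbation, so full follow-up for everyone is not what the article plans; about 330 prompts is the figure under the assumed rate.

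**What to change.** 1. Change the Theoretical Framework sentence so that alert-triggered ERS results are reported as the share of alerts confirmed (PPV) and as false alerts per monitored participant-day, with the share of prompts left unanswered.

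2. State that sensitivity and specificity are estimated over all monitored time against exacerbations found independently of the alert, from sources already planned: patient report to a clinician, consented medical records and the daily symptom questionnaires. Table 1 also lists an event diary as a label, but Table 2 does not include it, so it should not be relied on unless it is actually collected.

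3. Optionally, send the same ERS on randomly chosen no-alert days at a known rate, worded so that it does not reveal whether the algorithm fired, and weight by the inverse of that rate. Using the same neutral wording after alerts would also reduce the cueing.

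**Cost.** Items 1 and 2 need only a wording change and a link between data already collected. Item 3 needs a random-prompt rule in an app that already sends dynamic notifications, plus about one short questionnaire per participant per week. Table 4 already rates patient fatigue a medium risk, so the burden deserves thought. Item 3 mainly supports specificity, because a weekly random prompt will seldom fall on a missed exacerbation. It must start while data are being collected, since the ERS is valued for not relying on recall and such labels cannot be obtained afterwards.

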**Figure 1 figure1:**
[figure not shown]
Time course of symptoms and oximetry variables at exacerbation [11]. PEF: peak airflow.

**Table 1 table1:** Data analysis methods.

Data type	Methods	Labels
Active raw audio	MFCC^a^, SVM^b^, Adaboost	Questionnaires, tasks, spirometry
Passive wearable sensor	KNN^c^, least squares regression, Adaboost, HMM^d^	Questionnaires, tasks, event diary, spirometry
Multimodal sensor	DeepSense (CNN^e^+RNN^f^), GIR^g^, hierarchical HMM	Questionnaires, tasks, spirometry

^a^MFCC: mel-frequency cepstral coefficients.

^b^SVM: support vector machine.

^c^KNN: K-nearest neighbor.

^d^HMM: hidden Markov model.

^e^CNN: convolutional neural network.

^f^RNN: recurrent neural network.

^g^GIR: global iterative replacement.

### Aims

Our goal is to investigate the acceptability and feasibility of remote monitoring of patients with pulmonary disorders for the quantification of symptoms, understanding of the disease trajectory, and detection and prediction of clinically important events, such as exacerbations, in the following three disorder areas: COPD, ILD, posthospitalization COVID.

### Objectives

#### Primary Objective

The primary aim of the study is to evaluate cardiopulmonary disorders as potential targets for real-time, continuous, real-world remote monitoring. This study will investigate the potential benefit, acceptability, and feasibility of multiparametric remote monitoring of patient symptoms and physiology using commercially available wearable sensors for HR, activity, and SpO_2_; spirometry; phone sensors; questionnaires; and digital tests in patients with a range of pulmonary disorders.

The evaluation will be based on patient acceptability, dropout rates, and interpretation of data; detection of clinically important events, such as exacerbations and disease progression; quantification of symptoms (physical and mental health); impact of the disease on mood and well-being/QoL; and trajectory tracking of main outcome variables, symptom fluctuations, and order.

#### Secondary Objective

The secondary objective of this study is to provide data for power calculations [26] for a follow-on study. Power calculations will be centered around understanding the number of exacerbations according to sample size and duration. The power is effectively how good the signal is.

This will help plan future studies where we need to decide the sample size and duration to obtain accurate and acceptable exacerbations and the data associated with them.

### Outcomes

#### Acceptability of the Remote Monitoring System in the Three Disease Areas

The acceptability of the platform will be determined in terms of recruitment, retention, data completeness, and the qualitative experience of participants. The exit survey Technology Assessment Model Fast Form (TAM-FF) will also be used to evaluate the data collection infrastructure with participant feedback. The study will test both the feasibility and acceptability of tasks for participants. On completion of the data collection period, we will measure the total available data as a function of a theoretical maximum and assess data quality measured by a range of criteria, including missingness and contiguity.

#### Assess the Potential of Remote Monitoring in COPD, IPF, and COVID-19

The potential of remote monitoring will be evaluated in the context of cardiopulmonary disorders. This will involve developing methods to quantify disease trajectory as compared with standard clinical measures (in IPF, these would be changes in forced vital capacity and death); detecting exacerbations/symptoms, such as changes in wearable data (eg, HR, SpO_2_, and activity), during the reported period of exacerbation (a real-time algorithm will be included to predict exacerbations with patients notified with the ERS to confirm the prediction at or close to the time of the event); detecting exacerbations prior to or after the reported period of exacerbation (eg, a signal that may precede participant awareness of the exacerbation/symptom); detecting subclinical exacerbations in patients with lung fibrosis; tracking self-reported symptoms and outcomes (including precursor presymptomatic signals) and their frequency and order; and reporting longitudinal mental health symptom measures, as reported by the Generalized Anxiety Disorder scale (GAD-7) and Patient Health Questionnaire depression scale (PHQ-8), associated with the three diseases. This will provide the potential to assist with future applications around disease self-management. In the case of the posthospitalization COVID cohort, we will assess whether remote monitoring can be used as a symptom collection tool and as a long-term low-burden monitoring solution. Fatigue will be assessed by Garmin Body Battery values and the Fatigue Severity Scale, while long-term COVID impairments will be measured weekly using the Centers for Disease Control and Prevention (CDC) COVID-19 long-term effects (CCLTE) list, World Health Organization (WHO) symptoms list, and post-COVID functional status (PCFS), a COVID-19-specific widely used questionnaire on health-related impairments (physical functioning scale).

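### The participant's confirm-or-reject answer at the moment of an alert should not be the only stated yardstick for an algorithm described as predictive

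*Protocol article*

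**What the plan says.** All of this is in the Protocol article.

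- **Theoretical Framework.** Once the detection algorithm is running, "participants will be asked in near real time to confirm/reject and score the algorithm’s assertion via a short questionnaire", namely the ERS. The section goes on: "The ERS scoring will be used to evaluate the algorithm sensitivity/specificity". The intended timing is "close to or during the period of exacerbation, in order to provide accurate feedback independent of recall".
- **Outcomes, Assess the Potential of Remote Monitoring in COPD, IPF, and COVID-19.** The relevant text is "a real-time algorithm will be included to predict exacerbations with patients notified with the ERS to confirm the prediction at or close to the time", meaning when the exacerbation occurs. This stands in parentheses under detection within the period that the participant reports. Two further items follow separately: detection before or after that period, with the example "a signal that may precede participant awareness of the exacerbation/symptom", and "detecting subclinical exacerbations in patients with lung fibrosis".
- **Data Analysis.** The real-time ERS answers serve to assess the detection model and to "refine an individual-level model for exacerbation detection".
- **Study Flow Chart.** The ERS goes out when the processed data cross a threshold.

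None of these sections describes a later re-check of a rejected alert, a period within which a later onset would credit it, or a rule for an alert that is rejected and then followed by an event.

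**The concern.** An alert is triggered by physiology, not by symptoms. Theoretical Framework itself cites earlier COPD work in which resting heart rate, SpO2 and peak airflow correlated with symptoms before exacerbation onset as well as during and after it. Some correct alerts may therefore reach a participant who still feels normal. That participant can honestly reject the alert. If the ERS answer is the reference, a correct early alert then counts against the algorithm.

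The error has a direction. Between two algorithms that detect the same events, the one that fires later, when symptoms are plain, would look better. If rejections also enter the individual-level refinement as negative labels, they would push against early firing. Event detection is one of the bases on which Primary Objective says the study will be evaluated, so a biased reading could misinform the follow-on study.

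**Working it through.** The article gives no alert rate, predictive value, sensitivity or specificity, so there is no figure of the plan's own to reproduce. The check has two parts.

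**1. Reading the sections together**

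- What the algorithm does: it predicts (Outcomes), on wearable sensor data in real time, after training on previous days, initially 21 (Data Analysis).
- What triggers the ERS: a data threshold (Study Flow Chart). That the ERS falls close to or during the event is an expectation; the trigger does not guarantee it.
- What judges the alert: the participant's answer (Theoretical Framework, Data Analysis).
- What other labels exist: Table 1 names questionnaires, tasks, an event diary and spirometry for the passive-sensor methods, and Data Analysis plans to characterize the period before an exacerbation. Neither is linked to the scoring of ERS alerts.

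A correct alert that comes before awareness therefore has no described route to being credited once it has been rejected.

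**2. Size, under assumed values**

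Let q be the share of correct alerts that are rejected because the participant is not yet aware of the event. Assume that other correct alerts are confirmed and false alerts are not. Then

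apparent PPV = true PPV × (1 − q).

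| Assumed true PPV | q = 0.25 | q = 0.50 | q = 0.75 |
|---|---|---|---|
| 0.50 | 0.375 | 0.25 | 0.125 |
| 0.70 | 0.525 | 0.35 | 0.175 |
| 0.90 | 0.675 | 0.45 | 0.225 |

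For specificity per patient-day, assume 20 participants × 180 days = 3600 patient-days, with 20 correct and 20 false alerts, one per day. Days without an alert or event number 3600 − 40 = 3560. Rejected correct alerts move into the false positives:

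apparent specificity = 3560 / (3560 + 20 + 20q).

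- q = 0: 3560/3580 = 0.9944
- q = 0.75: 3560/3595 = 0.9903

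The damage falls on PPV. Per-day specificity hardly registers it. The effect on sensitivity cannot be worked out, because the article does not say how events without an alert enter the calculation.

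**The case against.** The strongest reply is that the article keeps these matters apart. The ERS-checked algorithm is listed under detection within the reported period, and the ERS is meant to arrive near or during the event. Detection before awareness and subclinical detection are separate items that do not mention the ERS. Independent labels and a pre-exacerbation analysis are planned. The ERS is also scored and sent on demand, so a persisting signal could trigger a second one. Algorithm details are referred to Multimedia Appendix 1, which is not shown.

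Much of this stands, and it rules out several stronger readings that a reader might infer:

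- *That the algorithm must fire before the participant notices.* No section says so. The COPD aim under Participant Cohorts is to be earlier than the patient's report to a clinician, which is not the same as earlier than awareness.
- *That rejected alerts are classed as false alarms.* No section states this. It is an inference from the ERS being the only stated basis for sensitivity and specificity.
- *That subclinical alerts must score zero.* Nothing says the ERS will judge them, so there is only a caution here: it should not.
- *That early detection will be trained away.* How ERS answers enter the refinement is not described. COPD follow-up ends at the first exacerbation, which limits what refinement could do for such a participant.

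What the reply does not remove is the use of the word predict for the same algorithm, a trigger that cannot tell whether symptoms have begun, and the absence of any link between the other labels and the scoring of alerts.

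**Conclusion.** The point holds in a limited form. The article evaluates and refines a predictive alert with an instant participant answer and states no other reference for its performance. An alert that correctly precedes awareness can be rejected and would then count against the algorithm. Apparent PPV falls by the fraction q, and per-day specificity changes little. The direction follows from the design. The size does not, because q, the true PPV and the number of alerts are all unknown and every figure above is an illustration. The conclusion also assumes that the unseen appendix and full protocol contain no rule for re-checking rejected alerts.

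Severity is moderate: event identification is an exploratory part of a feasibility pilot with 20 participants per cohort.

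**What to change.** In Theoretical Framework and Data Analysis:

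1. State that the instant ERS is not the sole reference for the algorithm's performance.
2. Score each alert also against an event onset defined independently of that ERS, from data already planned: daily CAT or L-IPF, daily spirometry and finger SpO2, and clinical or GP records. No measure that feeds the algorithm should also define the onset.
3. Fix in advance a look-ahead window after the alert, with other lengths as sensitivity analyses (for example 7 days, with 3 and 14). The length is the sponsor's choice; a longer window also credits more alerts by chance, which is why several should be shown.
4. Report ERS-confirmed and window-confirmed results side by side.
5. Do not use a same-day rejection as a negative label for refinement until the window has closed.
6. Say that the ERS will not be used to judge putative subclinical events.

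A repeat ERS at the end of the window after a rejection is optional and adds slight participant burden. The main change needs no new data. Its cost is added analysis wording and a short delay, about a week with a 7-day window, before a rejected alert can be used for refinement.
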